### Intervention group

To facilitate the development of the intervention and to ensure adherence to its timeline, the implementation of the intervention will be organised into four stages.

#### Stage 1

##### Intervention development

A literature review of nutrition and physical activity community based interventions for mothers with young children, pregnant and postpartum women has been conducted and will be continuously updated. Relevant behaviour change theories reviewed including the Social Cognitive Theory (SCT) [40], Transtheoretical Model (TTM) [41] and motivational interviewing [42] will support the development of a multi-strategy intervention [43]. Previous qualitative data obtained from Perth playgroup mothers will be used to ascertain the barriers and facilitators to healthy eating and being physically active, as well as their preferred intervention strategies [44]. The Precede-Proceed model will be used to organise the behaviour change theories and formative research data into an appropriate nutrition and physical activity behaviour change program [45,46].

#### Stage 2

##### Recruitment of staff

The program will be staffed by Health Science graduates, who will deliver the face-to-face workshop styled information and skill building sessions. Recruitment of the health promotion, nutrition and sport science graduates will be conducted via local universities and relevant professional associations.

#### Stage 3

##### Staff training

Staff will receive intensive training on the application of the Australian dietary and physical activity guidelines [31,32], and behaviour change theories including motivational interviewing. They will receive a comprehensive training manual on the delivery of the face-to-face workshop sessions. The staff will also receive ongoing support via email and phone by an accredited dietician, human movement specialist, health promotion specialist and the project coordinator.

#### Stage 4

##### Delivery of intervention in playgroup settings

The intervention will be delivered over six months. Interventions that aim to address multiple risk factors such as nutrition and physical activity show more positive outcomes when multiple intervention strategies are used to reach the target audience [43,47]. Hence the intervention group participants will receive four strategies: face-to-face workshop information and skill development session; mailed or emailed newsletters; SMS reminders on the main messages of the REFRESH program; and a home-based component.

##### Delivery of face-to-face workshops

The intervention group participants will receive six workshop sessions over six months (one session a month). Each session will be conducted for 30 minutes by project staff during the playgroup session at the playgroup venue. Workshops will focus on enhancing knowledge, attitudes and skills to enable informed decision making about nutrition and physical activity behaviours (Table 1).

**Table 1 T1:** REFRESH Intervention

Session (Week)	Session Details	Participant resources/interactive activities
1 (Week 1)	1. Introduction to Refresh Program 2. Overview of healthy eating and being physically active 3. Focus nutrition: fruits, vegetables and water • Guidelines • Benefits/barriers/overcoming barriers	1. Resources: • Program booklet • Healthy recipe booklet • Session one information summary pamphlet 2. Interactive activity: • Determine participant program needs

2 (Week 5)	1. Focus behaviour change: • Stages of change • Goal setting: long and short term goals 2. Focus physical activity: aerobic • Guidelines • Benefits/barriers/overcoming barriers 3. Focus nutrition: five food groups and 'extra' foods • Guidelines • Benefits/barriers/overcoming barriers	1. Resources: • Pedometer • Family dinner and physical activity planner (fridge magnet) • 'Extra' food record sheet • Session two information summary pamphlet 2. Interactive activity: • Playgroup 10,000 steps per day challenge

3 (Week 9)	1. Focus behaviour change: • Review established short term goals • Set new short term goals 2. Focus physical activity: Muscle strength and flexibility exercises • Guidelines • Benefits/barriers/overcoming barriers	1. Resources: • Muscle strength and flexibility exercise card (fridge magnet) • Physical activity diary • Session three information summary pamphlet 2. Interactive activity: • Muscle strength and flexibility exercises • Integrated exercises "

4 (Week 13)	1. Focus behaviour change: • Review established short term goals • Set new short term goals 2. Focus nutrition: • Healthy eating messages • Menu planning • Food label reading • Making sense of nutritional claims	1. Resources: • Shopping list with healthy shopping tips • Comparing packaged food per 100 g (fridge magnet) • Session four information summary pamphlet 2. Interactive activity: • Reading packaged food labels • Developing a daily menu

5 (Week 17)	1. Focus behaviour change: • Review established short term goals • Set new short term goals • Overcoming relapses 2. Focus nutrition: fats and sugars • Recommended intake • Benefits/barriers/overcoming barriers	1. Resources: • Session five information summary pamphlet 2. Interactive activity: • Modifying recipes • Healthy cooking methods

6 (Week 21)	1. Focus behaviour change: • Review established short term goals • Social support 2. Focus nutrition: Fibre and Glycemic Index • Recommended intake • Benefits/barriers/overcoming barriers	1. Resources: • Session six information summary pamphlet 2. Interactive activity: • Modifying recipes • Healthy cooking methods

##### Delivery of newsletters

The intervention group participants will receive six newsletters via post or email over six months (one newsletter a month, one week after each face-to-face workshop session). The newsletters will be in an informal format and will contain myth dispelling information on nutrition and physical activity.

##### Delivery of SMS reminders

The intervention group participants will receive 18 SMS reminders via mobile phones over six months (reminders to attend the face-to-face workshop sessions and nutrition and physical activity motivating messages).

##### Delivery of home based component

The intervention group participants will receive home based resources at each of the face-to-face workshop sessions to support the content of the REFRESH program. The home based components will include a specially tailored program booklet, pedometer, menu planner fridge magnet, a shopping list with food label reading tips, a muscle strength and flexibility exercise chart fridge magnet, a physical activity diary and an 'extra' food record sheet. The workshops will offer an opportunity for these resources to be explained and for questions to be answered.

### Control group

The control group participants will not receive any intervention materials. Their only contact with the project will include completing the questionnaires at the three data collection periods.

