**Methods/Design:**

The current study is a randomized controlled trial lifestyle (nutrition and physical activity) intervention for mothers with children aged between 0 to 5 years attending playgroups in Perth, Western Australia. Nine-hundred participants will be recruited and randomly assigned to the intervention (n = 450) and control (n = 450) groups. The study is based on the Social Cognitive Theory (SCT) and the Transtheoretical Model (TTM), and the Precede-Proceed Framework incorporating goal setting, motivational interviewing, social support and self-efficacy. The six month intervention will include multiple strategies and resources to ensure the engagement and retention of participants. The main strategy is home based and will include a specially designed booklet with dietary and physical activity information, a muscle strength and flexibility exercise chart, a nutrition label reading shopping list and menu planner. The home based strategy will be supported by face-to-face dietary and physical activity workshops in the playgroup setting, posted and emailed bi-monthly newsletters, and monthly Short Message Service (SMS) reminders via mobile phones. Participants in the control group receive no intervention materials. Outcome measures will be assessed using data that will be collected at baseline, six months and 12 months from participants in the control and intervention groups.

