### Sample size determination

In order to detect a 20% difference in physical activity at 80% power and 5% level of significance, sample size of 310 mothers of young children are required at the 6-months post-intervention survey in each of the intervention and control groups. A small effect size (0.2) [37] is assumed for studies on behavioural effects due to the influence of extraneous variables and the subtleties of human performance. Allowing for an attrition rate of 30%, 900 mothers of young children will be recruited into the study. Sample size calculations were determined using Power Analysis and Sample Size software [38].

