### Data collection

Process data will be collected during the implementation of the intervention. The playgroup is a novel setting for the recruitment and delivery of health promotion interventions for mothers with young children. Therefore, the process evaluation will be a key component of the program's evaluation. This will be conducted with both the participants and the project staff, providing two perspectives on the program delivery and content.

Outcome data will be collected at baseline, six months and 12 months. At baseline control group participants will be hand delivered a self-completion questionnaire at the playgroup along with a self-addressed envelope and measuring tape to record waist and hip measurements. The intervention group will be provided all of the above and a pedometer to record the number of steps taken each day. At six months the control group participants will be hand delivered a self-completion questionnaire at the playgroup along with a self-addressed envelope. The intervention group will be provided all of the above and a pedometer to record the number of steps taken each day. At 12 months the control and intervention group participants will be posted a self-completion questionnaire with a self-addressed envelope.

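### Contact said to serve retention goes to the intervention arm only, which creates a foreseeable risk of unequal drop-out, mainly at six months

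*Protocol article*

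**What the plan says.** **Control arm.** The Control group section excludes intervention materials and adds: "Their only contact with the project will include completing the questionnaires at the three data collection periods".

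**Intervention arm.** There is one workshop a month for six months (Delivery of face-to-face workshops). On newsletters: "The intervention group participants will receive six newsletters via post or email over six months". On text messages: "The intervention group participants will receive 18 SMS reminders via mobile phones over six months". The SMS section gives these messages two purposes, workshop attendance and motivation. The Abstract says of the whole package: "The six month intervention will include multiple strategies and resources to ensure the engagement and retention of participants".

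**Outcome collection (Data collection).** For controls: "At six months the control group participants will be hand delivered a self-completion questionnaire at the playgroup along with a self-addressed envelope". For the other arm: "The intervention group will be provided all of the above and a pedometer to record the number of steps taken each day". At 12 months both arms are posted the same form. No reminder to return a questionnaire is described for either arm.

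**Attrition and analysis.** Sample size determination requires 310 mothers per arm at six months with an effect size of 0.2, and then: "Allowing for an attrition rate of 30%, 900 mothers of young children will be recruited into the study". No split by arm is given. Statistical analysis names multi-level repeated measures and logistic regression.

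**The concern.** The protocol ties retention to the programme, and only one arm receives the programme. The Control group section reads as a restriction, not merely as silence. Taken at face value, it leaves no room for a keep-in-touch contact with controls between baseline and six months, or between six and 12 months.

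Outcome data depend on mothers filling in a form and sending it back, so how connected a mother feels to the project could plausibly affect whether she does so. By six months, staff have been visiting intervention playgroups monthly (the last workshop is in week 21), while control mothers have had no project contact since baseline. At 12 months the form goes by post, so return depends on a current address, and only the intervention arm's contact details are described as being used in the meantime.

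If drop-out differs by arm and is related to outcome, the mothers left in the two arms are no longer comparable. The planned effect is small, so a modest distortion counts. The Abstract also says the trial will add evidence on retention. Under this design, retention by arm would partly reflect unequal contact.

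**Working it through.** **1. Scheduled contacts before the six-month form.** The body of the article gives 6 workshops + 6 newsletters + 18 SMS = 30. The Abstract describes SMS as monthly and newsletters as bi-monthly. At its lowest reading (newsletters every second month) that is 6 workshops + 6 SMS + 3 newsletters = 15. Controls have 0 between waves on either reading.

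**2. The plan's own attrition figure.** For a standardised effect of 0.2 and 80% power, n per arm = 2(z_α + z_β)²/0.2².
- One-sided 5%: 2(1.645 + 0.842)²/0.04, which gives 310, matching the plan.
- Two-sided 5%: 393.
- Attrition: 310/(1 − 0.30) = 443 per arm, or 886 in total; the plan states 900.

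The attrition arithmetic is sound. Sidedness is not stated in the plan and is a separate matter.

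**3. Bias from unequal loss.** Let p be the proportion lost in an arm and D the mean of returners minus the mean of non-returners, in SD. The returners' mean then exceeds the full-arm mean by p × D, so

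bias (intervention − control) = p_I × D_I − p_C × D_C.

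The document gives neither p by arm nor D. The values below are assumptions: overall loss is held at the planned 30%, D is the same in both arms, and D is read as what remains after the model has used the observed data.

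| Loss, intervention / control | D = 0.3 | D = 0.5 |
|---|---|---|
| 30% / 30% | 0 | 0 |
| 25% / 35% | −0.10 × 0.3 = −0.03 SD | −0.10 × 0.5 = −0.05 SD |
| 20% / 40% | −0.20 × 0.3 = −0.06 SD | −0.20 × 0.5 = −0.10 SD |

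Against the planned 0.2, the four non-zero cells are 15%, 25%, 30% and 50%. The minus sign means that if controls lose more and returners are the more active, the bias works against the intervention. If the intervention arm loses more, the sign reverses.

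**4. Power.** Two-sided power is Φ(0.2/√(1/n_I + 1/n_C) − 1.96), treating mothers as independent.
- 30% / 30%: 450 × 0.70 = 315 in each arm; 70.9%.
- 25% / 35%: about 338 and 292; 70.7%.
- 20% / 40%: 360 and 270; 70.0%.

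An uneven split at the same overall loss costs under one percentage point.

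**5. A case that equal contact would not cure.** With equal 30% loss but opposite selection in the two arms, the bias is 0.30 × 2 × D, which is 0.18 SD at D = 0.3. This arises from who leaves, not from how many leave.

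**The case against.** The case on the other side is substantial.

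- **The contact is the treatment.** Workshops, newsletters and SMS are what is being tested against no intervention, so contact must differ by arm. This stands. The point is only that retention contact has not been separated from programme contact.
- **Outcome collection is nearly parallel.** Both arms are handed the form at the playgroup at six months and posted it at 12 months. The only stated difference at six months is the pedometer. Playgroups meet weekly, so controls remain in the setting where the six-month form is delivered. This stands and lowers the risk.
- **The control restriction can be read more loosely.** Contact for completing questionnaires could cover reminders to return them, and postal details must be held for both arms. This stands in part: a contact between waves remains excluded on a plain reading. Retention in the Abstract may also mean staying in the programme rather than in follow-up.
- **The model may absorb some of it.** A likelihood-based repeated-measures analysis tolerates loss explained by observed data, so unequal loss alone does not bias it. This stands. However, a mother lost before six months contributes baseline data only, which limits what the model can adjust for.
- **The direction is open.** Workshop burden could raise loss in the intervention arm instead. This stands.

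A reader might go further and infer that intervention mothers are chased harder for their questionnaires. The documents do not say so: the SMS have other stated purposes, and no questionnaire chasing is described in either arm.

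**Conclusion.** Contact is asymmetric by design, and the protocol itself links that contact to retention. This makes differential attrition a foreseeable risk. The risk is greatest at six months. It is weaker at 12 months, because the described programme contact ends at six months and the final form is posted identically to both arms.

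The illustrative shift of 0.03 to 0.10 SD rests wholly on assumed values: a 10 to 20 point difference in loss, and a 0.3 to 0.5 SD difference between returners and non-returners, equal in both arms and left over after model adjustment. With equal loss and the same selection in both arms the shift is zero.

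Two stronger readings are tempting but unsupported. One is that both follow-up comparisons will be biased; neither unequal loss nor its dependence on outcome can be established from the documents. The other is that 270 control returns, in the 20% / 40% case, fall materially short of the required 310. In the same case the intervention arm has 360, and power barely moves. Nor is a single 30% allowance an error; it is ordinary planning and does not claim that loss will be equal.

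This is therefore a worthwhile, inexpensive improvement to the design and not the correction of a demonstrated bias.

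**What to change.** Amend the Control group section so that questionnaire-related contact is defined separately from the programme and is identical in both arms:

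- one contact-detail check between waves, with no nutrition or activity content;
- the same number of reminders to return the six- and 12-month forms, by the same channels and on the same schedule;
- mobile, email and postal details collected from both arms at consent;
- attrition at six and 12 months reported by arm.

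The no-intervention comparison is kept, because nothing sent to controls carries programme content. The cost is one change of wording, minor messaging and postage through channels the trial already uses, and a few neutral contacts for controls. The change should reduce loss and the chance that it differs by arm. It will not remove selection that comes from mothers disengaging from the programme itself, so attrition by arm still needs to be examined when the results are read.

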### Process measures

#### Participant process evaluation

The REFRESH booklet will be assessed by the participants in terms of attractiveness, comprehension, personal relevance, believability, and legibility [48]. Workshop and staff feedback sheets will be provided to participants to assess the content and workshop delivery methods in the playgroup setting. Participants will be invited to comment on the REFRESH program's impact on their physical activity and nutrition behaviours and to provide suggestions for improvements to the intervention [49].

#### Staff process evaluation

The staff will provide feedback on the playgroup as a setting for health promotion programs. This evaluation will focus specifically on the playgroup characteristics, and the skills deemed necessary to deliver workshops in this setting. Staff will also provide feedback on working with mothers as a target group within the playgroup setting, what the mothers want to learn about nutrition and physical activity and common myths mothers report. Staff will also maintain a diary of their perceptions related to the delivery of the face-to-face workshop sessions, and responses by participants to the session content and activities.

### Outcome measures

The self-administered questionnaire will be comprised of instruments which have been previously validated and tested for reliability [50-52], and will undergo further reliability testing prior to its use at baseline.

Physical activity will be measured by The International Physical Activity Questionnaire (IPAQ) [53]. This instrument has been accepted as the physical activity measurement tool in many settings and is specifically designed for population-based prevalence studies. Muscle strength exercise assessment will be based on recommendations from the American Heart Association and Australian physical activity guidelines [54]. Physical activity knowledge will be assessed by a modified version of the American Adult's Knowledge of Exercise Questionnaire [55]. Dietary intake will be measured using a modified version of the Fat and Fibre Barometer [56]. The New South Wales Government questionnaire will be used to measure soft drinks, fruit juice and snack consumption [57]. Added sugar consumption will be assessed using the 2005 National Health Interview Survey [58]. Nutrition knowledge will be assessed by a modified version of the General Nutrition Knowledge Questionnaire [59].

Self-efficacy for nutrition and physical activity behaviours will be assessed. Nutrition and physical activity self-efficacy will be assessed using items from previously validated instruments [52]. Validated questions will also confirm participants' stages of change regarding fruit and vegetable consumption [60]. Social support for physical activity will be assessed based on items from the Sallis et al. instrument [51].

General physical and mental health will be measured by The Medical Outcomes Study Short-Form Health Survey (SF-8) [61]. SF-8 is a standard international generic instrument of health status. It comprises two summary scales - the physical component summary (PCS) score and the mental component summary (MCS) score.

Demographic characteristics will include gender, age, educational level, country of birth, marital status, socioeconomic status, financial status and co-morbidities. Anthropometric measures will include self-reported height and weight, waist and hip girth. A recent study has confirmed that self report measures are suitable for such studies when a correction factor is applied [62].

Height, weight, waist and hip girth measurements will be conducted by research staff on a random subsample of 100 participants from the intervention group. Calculations of differences between self reported and research staff measured data will be undertaken to identify a correction factor based on the methodology of Dhaliwal et al. [62].

## Ethics

The project protocol has been approved by the Curtin University Human Research Ethics Committee (approval number HR 186/2008).

## Discussion

The REFRESH project is unique in using playgroups for a lifestyle intervention. The playgroup environment is an innovative setting for health promotion for mothers with young children, as it offers an exciting avenue to reach this target group and support behaviour change. The recruitment of participants through playgroups is beneficial as it will encourage all playgroup members to register for the program, thereby not just recruiting those who are motivated to adopt health enhancing behaviour [63].

The program will provide an opportunity for a variety of strategies to be implemented and evaluated. This evaluation data will be collected from participants in their own communities and not in a research centre, making the program relevant to the community based population and not just a clinical group. The project will provide guidelines for the development, implementation and evaluation of a minimal intervention home-based tailored physical activity and nutrition program. The information gathered will be valuable in helping to identify and address the barriers to participating in physical activity and nutrition programs for this target group. The project has the potential, to reduce chronic disease and enhance mental health for mothers of young children in the playgroup setting.
